### Interventions

#### The Daily Exercise Program

The daily walking exercise program was designed based on both Dutch and European PA guidelines for the prevention of cardiovascular diseases and its rehabilitation [34,35], and also in compliance with expert opinions from physiotherapists at CZE. The program consists of 2 walking exercises and 1 overall goal for the amount of PA per day, with increasing intensity over the duration of the trial. The restricted durations of each walking exercise session are between 5 and 15 minutes for the first week, 10 and 20 minutes for the second week, and 15 and 25 minutes in the third week. The exact duration in each week will be decided by the patients and their physician together in the introduction meeting, adapted to the physical conditions of the patients after surgery (see Figure 2 for an example). Patients are also told to continue the same walking exercise after the 3-week study as long as the exercise plan does not conflict with their formal CR program.

One feature of the program is that patients will be encouraged to execute the 2 daily walking exercises at the same time and in the same context throughout the weeks. According to psychological theories of habit [36], performing the exercise in this way facilitates the formation of a strong exercise habit through the repetition of the behavior in the same environment. Based on the idea of implementation intention [37], patients will be asked to decide the time and context themselves according to their existing daily routines, and to imagine themselves performing the walking exercises in that context for 1 minute. This feature was used not only to prevent patients from omitting the exercise, but also to potentially promote a habit of exercising after the trial. The daily exercise program will be introduced to the intervention and the control group indifferently, and a booklet of the planned program will be distributed to all patients.

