### Sample Size Calculation

We used a minimum effect size of interest approach to calculate the sample size needed to detect a statistically significant difference between the intervention group and the control group in terms of the primary outcome (average daily steps over 3 weeks). In an internal discussion between researchers, physicians, and CR experts at CZE, a 2000-step daily difference was proposed to be the minimum effect size of interest, and a 3000-step within-group standard deviation was assumed based on [32]. These assumptions amount to a moderate to strong effect size in terms of Cohen *d* of 0.67, which is justifiable given the large differences between the two conditions in terms of costs. Based on a simulation study in the R statistical programming environment [33], 100 participants (50 in each group) are required to have a 90% power to detect the effect at a significance level of .05. Because we will also have day-level data for steps over 3 weeks, multilevel regression models can also be used for examining the differences in PA between the two groups, which should have much higher power due to the large number of observations (ie, data collected over 21 days by 100 patients). Details of the simulation-based power analysis (and the R code) can be found in Multimedia Appendix 2.

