#### The Mobile-Based Coaching App

Patients in the intervention group will also be monitored and coached by nurse practitioners through an e-coaching app called Heart Angel, which is a customized version of the commercial Virtuagym platform [38]. We decided to use this particular app because (1) the platform meets our needs for e-coaching and is free; (2) a customized version tailored to the context of CR was made available; and (3) the platform works seamlessly with the Neo Health One self-tracking device. The nurse practitioners work at the same cardiac surgery department at CZE and are known by the patients during their stays at the hospital, and they receive a 1-day training to use the platform provided by the researchers. The patients will use a mobile version of the Heart Angel app, while the nurse practitioners will use an associated web platform for coaching.

The Heart Angel app serves the following functions. First, the daily walking exercise program is saved and shown in the app, so the patients can always open it to review their goals and plans (Figure 4B). Second, data from the self-tracking device are transmitted to the app, so both patients and their coaches (the nurse practitioners) can monitor their PA performance using the app (Figure 4C). Third, the mobile app sends daily notifications in the morning to remind the patients of their planned daily step goals, and whenever a goal is reached, they receive achievement badges from the app. Fourth, when there is a need to contact their coach, the patients can send messages through the mobile app (Figure 4D). Conversely, the nurse practitioners are asked to closely monitor their patients’ compliance and performance, and to coach them whenever needed through the app, for example, to check for problems if a patient is not exercising sufficiently according to the plan, or to compliment a patient who is doing well. As the above functionalities are prototypical for e-coaching platforms in general, our RCT is meant to be an evaluation of the general functionalities of e-coaching rather than the Heart Angel app per se.

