### Primary and Secondary Outcomes

The primary outcome is the amount of daily physical activities by the patients, operationalized as the average daily steps over the 3 weeks. The steps are measured by the Axivity AX3 tracker, which is a CE-marked 3-axis logging accelerometer developed by the Open Movement organization at Newcastle University (Figure 5). The device is intended to be used in research on activity recognition, motion measurement, medical research, and movement science. It has been used previously in a large-scale clinical trial in UK [39] and validated for measuring PA in older adults [40]. Patients in both intervention and control group will be asked to wear the device as a clip on their cloths at their hip on the nondominant side (eg, a belt clip). The device has a long battery life (around 1 month) and large internal memory (1-month’s data with a sampling frequency of 50 Hz), so the patients do not have to worry about charging the device or offloading the data. Unlike the self-tracking device (the Neo Health One), this measurement device only records data but provides no feedback about steps to the patients.

In addition to the primary outcome, 2 secondary outcomes are used to test whether the behavioral-level increase of daily PA levels would bring patients benefits at physical and psychological levels for their preparations for the formal CR program. To measure physical fitness, a bicycle ergometer test will be held for each patient at the Cardiac Function Department as their usual clinical practice within 1 week after the 3-week trial. The research team will not be involved in the administration of the test, but 3 parameters of interest, namely, peak oxygen uptake (peak VO_2_), maximal workload, and maximum heart rate (HR_max_), will be provided to us. Previous studies have shown positive effects of walking trainings on physical fitness [41-43]. However, because of the short duration and moderate intensity of our exercise program, we do not strongly predict significant effects given the sample size.

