### Patient Timeline

Patient timeline in this RCT is illustrated in Figure 6. During the preoperative screening in the outpatient clinic, patients are informed about the study and are given 1-2 weeks to make their participation decisions. If they agree to participate, a consent form is signed a few days before the surgery. After the surgery and the 3-5-day monitoring at the hospital, an introduction meeting with a nurse practitioner is held at discharge. In this meeting, the study goals and procedure are introduced first, and then the daily walking exercise program is explained and details are planned together with the patients. After the randomized group allocation, according to the assigned group, patients are handed the devices and are guided through the installation, registration, and use of the devices and the mobile app. After returning home, patients are expected to follow the exercise program at home for 3 weeks, before they are referred to the conventional CR program. Right after discharge and at the end of each study week, a questionnaire is sent to the patients by email to measure the variables of interest discussed above. After the 3-week trial, a bicycle ergometer test is scheduled to take place at the hospital within 1 week, where patients also return the devices. A final questionnaire is sent 1 week after the study to measure the same set of variables to explore the prolonged effects of the exercise program on patients’ psychological states. Eight patients from the intervention group will be randomly selected for an additional interview about their experience with the devices and the mobile app.

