### Statistical Analysis

For the outcome variables of interest, that is, average daily steps, overall compliance rate, and physical fitness measured in the bicycle ergometer test (peak VO_2_, maximal workload, HR_max_), the following 2-step procedure will be used. In the first step, independent sample *t* tests (unpaired) will be used to compare the outcome variables between the two study conditions. Second, when potential confounding variables are identified post hoc, they will be added to multiple regression models to control for their influences. For step data at the day level, multilevel models will be built to test the same hypotheses, with patient ID as the grouping variable [55]. We will use the conventional α level of .05 to judge for statistical significance, and more importantly to use the estimated effect sizes in order to judge the clinical significance of the effects.

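### Planned walking minutes are fixed before randomisation and probably predict steps, yet the step comparison is unadjusted and takes covariates only post hoc, at a small cost in precision

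*Protocol article*

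**What the plan says.** The Daily Exercise Program section prescribes two walks a day. Each walk lasts 5 to 15 minutes in week 1, 10 to 20 in week 2 and 15 to 25 in week 3. Within those bands the length is individual and depends on how the patient is after the operation: "The exact duration in each week will be decided by the patients and their physician together in the introduction meeting, adapted to the physical conditions".

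The Patient Timeline section gives the order of the introduction meeting: "the daily walking exercise program is explained and details are planned together with the patients. After the randomized group allocation" come the devices and the app set-up. Randomization and Blinding agrees: allocation is generated after the programme has been introduced, and the nurse practitioner is blind to it until then.

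The primary outcome is physical activity, "operationalized as the average daily steps over the 3 weeks". Statistical Analysis sets out two steps: an unpaired t test between the arms, then multiple regression with whatever potential confounders are found post hoc. Day-level steps go into multilevel models grouped by patient. Planned duration is not named as a covariate in any of these.

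**The concern.** A variable that is set before allocation, reflects the patient's condition after surgery, and states how much the patient is told to walk is a natural covariate for a step count. Here it is passed over, while the stated rule lets other covariates in after the data have been seen. Two things are at stake. One is precision, because differences in steps that arise from different plans stay in the residual variance. The other is the standing of the adjusted result, because a covariate set chosen after the fact leaves room for selective choice that a named baseline covariate does not.

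**Working it through.** **1. The plan's own sample size.** Inputs from Sample Size Calculation: "a 2000-step daily difference was proposed to be the minimum effect size of interest", a within-group SD of 3000 steps, and "100 participants (50 in each group) are required to have a 90% power to detect the effect at a significance level of .05". Sidedness is not stated; two-sided reproduces the figure.

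- Normal approximation: n per arm = 2 × (1.960 + 1.282)² × (3000/2000)² = 47.3, so 48.
- Exact noncentral t: 49 per arm, 98 in all, against the stated 100.
- Power at 50 per arm: 0.915 (normal), 0.910 (exact t).

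The stated size is reproduced. The reference power below is 0.910.

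**2. Range of the plan.** Mean minutes per day = 2 × mean of the weekly session lengths.

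- Lowest: 2 × (5 + 10 + 15)/3 = 20.
- Highest: 2 × (15 + 20 + 25)/3 = 40.

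The span is 20 minutes a day, a ratio of 2.

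**3. From minutes to variance.** The article gives no cadence, so this is an assumption, taken over 60 to 120 steps per minute. Plans are assumed to be followed. Span in steps = 20 × cadence. The SD of dose is span/√12 if plans are evenly spread and each patient keeps the same relative place in the band every week. It is span/2, the maximum possible, if half the patients sit at each limit. Share = SD²/3000². After adjustment the residual SD is √(3000² − SD²), and power is recomputed with the exact t (ignoring the one degree of freedom spent).

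| Steps/min | Span | SD, even | Share | Power adj. | SD, extremes | Share | Power adj. |
|---|---|---|---|---|---|---|---|
| 60 | 1200 | 346 | 1.3% | 0.914 | 600 | 4.0% | 0.921 |
| 80 | 1600 | 462 | 2.4% | 0.916 | 800 | 7.1% | 0.928 |
| 100 | 2000 | 577 | 3.7% | 0.920 | 1000 | 11.1% | 0.938 |
| 120 | 2400 | 693 | 5.3% | 0.924 | 1200 | 16.0% | 0.950 |

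At 100 steps per minute the residual SD is 2944 (even) or 2828 (extremes), and 90% power would need 47 or 44 per arm instead of 49. If a patient's place in the band varied independently from week to week, the SD would fall to 333 and adjusted power would be 0.913.

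**4. Chance imbalance between arms.** SE = SD × √(2/50): 577 × 0.2 = 115 steps, or 1000 × 0.2 = 200 steps. The SE of the whole comparison is 3000 × 0.2 = 600 steps, which already contains this component.

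**5. If the dose differences came on top of the 3000-step SD.** The total SD would be 3055 (even) or 3162 (extremes) at 100 steps per minute. Unadjusted power would then be 0.900 or 0.879, and adjustment would bring it back to 0.910. The article does not show whether the cited SD already includes such differences.

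**The case against.** The strongest reply is that little is lost. Comparing randomised means does not require equal doses, tailoring belongs to the programme in both arms, and the trial meets its 90% target without adjustment. Entry is limited to patients at relatively low risk, so plans may cluster more tightly than an even spread. All of this stands, and it limits the size of the point.

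A second reply is that covariate lists belong in an analysis plan that is not shown. That would settle the matter if the article were silent. But it states a rule, post hoc choice, and its Expected Results section says the analysis will follow the method reported there. The point concerns that stated rule.

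Three stronger readings are tempting, and the document does not support them:

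- *That dose variation as large as the target effect is left as noise.* The 2000 steps are the gap between two patients at opposite limits, at 100 steps per minute with full adherence. What enters the t test is the SD, 577 steps and at most 1000 at that cadence.
- *That unequal doses bias the comparison.* The dose is fixed before allocation and then randomised over. A chance imbalance is part of the sampling error that the test already counts.
- *That control plans go unrecorded, or that an unblinded nurse enters the plan in the app.* The booklet goes to patients in both arms. The app section says only that "the daily walking exercise program is saved and shown in the app, so the patients can always open it to review their goals and plans", without saying who enters it or when. Neither claim can be drawn from silence in a condensed article.

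**Conclusion.** The point holds as a modest improvement to the stated analysis. A baseline variable that plausibly predicts the primary outcome is left out of the planned comparison, and adjustment is left to post hoc choice. The unadjusted test remains valid and unbiased.

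At 100 steps per minute the gain in power is about 1 percentage point with evenly spread plans (0.910 to 0.920) and at most about 3 (0.938). Over 60 to 120 steps per minute it runs from 0.4 to 1.4 points with an even spread, and reaches 4 points only at the far extreme. These figures assume that plans are followed and act on steps only through the prescribed walks. If planned minutes also track fitness that drives other walking, the gain could be larger; the document gives nothing from which to estimate that.

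**What to change.** Record each patient's three weekly session durations in the trial data, in both arms, before the randomisation program is run. In Statistical Analysis, name mean planned walking minutes per day as a prespecified covariate in the comparison of average daily steps and in the day-level multilevel model, replacing the post hoc choice of covariates.

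The cost is three numbers per patient and one degree of freedom. No patient's walking plan changes, and the sample size of 100 stands.

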**Figure 2 figure2:**
[figure not shown]
An example of a personalized rehabilitation plan for a patient.

#### The Self-Tracking Device

Patients in the intervention group will receive a Neo Health One wristband (Figure 3), which is a commercial and CE-marked self-tracking device with build-in accelerometers. Patients are instructed to wear these bands as much as possible during the day. They can review at any time the number of steps they walked on a specific day and the step data are also synchronized to the mobile-based coaching app used in the trial. Patients in the intervention group will be instructed to wear the device as a wristband on their nondominant side.

**Figure 3 figure3:**
[figure not shown]
The Neo Health One wristband as the self-tracking device in the study.

#### The Mobile-Based Coaching App

Patients in the intervention group will also be monitored and coached by nurse practitioners through an e-coaching app called Heart Angel, which is a customized version of the commercial Virtuagym platform [38]. We decided to use this particular app because (1) the platform meets our needs for e-coaching and is free; (2) a customized version tailored to the context of CR was made available; and (3) the platform works seamlessly with the Neo Health One self-tracking device. The nurse practitioners work at the same cardiac surgery department at CZE and are known by the patients during their stays at the hospital, and they receive a 1-day training to use the platform provided by the researchers. The patients will use a mobile version of the Heart Angel app, while the nurse practitioners will use an associated web platform for coaching.

The Heart Angel app serves the following functions. First, the daily walking exercise program is saved and shown in the app, so the patients can always open it to review their goals and plans (Figure 4B). Second, data from the self-tracking device are transmitted to the app, so both patients and their coaches (the nurse practitioners) can monitor their PA performance using the app (Figure 4C). Third, the mobile app sends daily notifications in the morning to remind the patients of their planned daily step goals, and whenever a goal is reached, they receive achievement badges from the app. Fourth, when there is a need to contact their coach, the patients can send messages through the mobile app (Figure 4D). Conversely, the nurse practitioners are asked to closely monitor their patients’ compliance and performance, and to coach them whenever needed through the app, for example, to check for problems if a patient is not exercising sufficiently according to the plan, or to compliment a patient who is doing well. As the above functionalities are prototypical for e-coaching platforms in general, our RCT is meant to be an evaluation of the general functionalities of e-coaching rather than the Heart Angel app per se.

**Figure 4 figure4:**
[figure not shown]
Screenshots of the Heart Angle mobile coaching app. (A) Homepage of the app showing the navigations to different functions. (B) Recorded walking exercise plan in the app in a calendar view. (C) Progress page showing the step data from the Neo Health One band. (D) An example of chatting between a patient and a coach.

### Primary and Secondary Outcomes

The primary outcome is the amount of daily physical activities by the patients, operationalized as the average daily steps over the 3 weeks. The steps are measured by the Axivity AX3 tracker, which is a CE-marked 3-axis logging accelerometer developed by the Open Movement organization at Newcastle University (Figure 5). The device is intended to be used in research on activity recognition, motion measurement, medical research, and movement science. It has been used previously in a large-scale clinical trial in UK [39] and validated for measuring PA in older adults [40]. Patients in both intervention and control group will be asked to wear the device as a clip on their cloths at their hip on the nondominant side (eg, a belt clip). The device has a long battery life (around 1 month) and large internal memory (1-month’s data with a sampling frequency of 50 Hz), so the patients do not have to worry about charging the device or offloading the data. Unlike the self-tracking device (the Neo Health One), this measurement device only records data but provides no feedback about steps to the patients.

In addition to the primary outcome, 2 secondary outcomes are used to test whether the behavioral-level increase of daily PA levels would bring patients benefits at physical and psychological levels for their preparations for the formal CR program. To measure physical fitness, a bicycle ergometer test will be held for each patient at the Cardiac Function Department as their usual clinical practice within 1 week after the 3-week trial. The research team will not be involved in the administration of the test, but 3 parameters of interest, namely, peak oxygen uptake (peak VO_2_), maximal workload, and maximum heart rate (HR_max_), will be provided to us. Previous studies have shown positive effects of walking trainings on physical fitness [41-43]. However, because of the short duration and moderate intensity of our exercise program, we do not strongly predict significant effects given the sample size.

Psychologically, we will examine whether patients in the intervention group report higher level of self-efficacy toward PA compared with the control group at the end of the third week. The rationale is that patients in the intervention group receive more guidance, social and emotional supports, and their ability to walk more steps may also increase perceived efficacy [44]. Based on a theory-based recommendation in [45], a scale for measuring self-efficacy in our context was developed specifically for this study and will be included in the 5 questionnaires sent to the patients (Multimedia Appendix 2).

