### Randomization and Blinding

Patients will be allocated to the intervention or control group through a computerized randomization procedure during the introduction meeting. Specifically, the procedure takes place after the introduction of the general study information and the daily walking exercise program, and before the tutorials about how to use the (condition-dependent) technologies. The timing of the randomization is designed to blind the experimenter (a nurse practitioner) to treatment allocation until the daily walking exercise program is fully introduced, in order to minimize potential biases in guiding and motivating the patients. As with most electronic health (eHealth) trials, patients in our trial are not blinded to their conditions. Assessors of the bicycle ergometer test will be blinded to the research purposes as well as treatment allocation.

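### The ergometer outcome consists of three effort-dependent end-of-test values from unblinded patients, so an arm difference in effort could be read as a difference in physical fitness

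*Protocol article*

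**What the plan says.** The fitness outcome is introduced in Primary and Secondary Outcomes: "To measure physical fitness, a bicycle ergometer test will be held for each patient". The test is part of usual care and takes place "within 1 week after the 3-week trial". The trial team does not run it but is sent results from it: "The research team will not be involved in the administration of the test, but 3 parameters of interest" are supplied. What the team receives is listed: "3 parameters of interest, namely, peak oxygen uptake (peak VO_2_), maximal workload, and maximum heart rate (HR_max_), will be provided to us".

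Statistical Analysis groups these three values as physical fitness and compares each between arms by unpaired t test. Regression adjustment follows if confounders are identified afterwards.

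On blinding, the Randomization and Blinding section says that "patients in our trial are not blinded to their conditions", and that "Assessors of the bicycle ergometer test will be blinded to the research purposes as well as treatment allocation".

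The section on the coaching app gives only the intervention arm reminders, badges, monitoring and compliments from a nurse. The article expects a psychological effect of this support, reasoning that "patients in the intervention group receive more guidance, social and emotional supports, and their ability to walk more steps may also increase perceived efficacy".

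The article names no effort marker, no submaximal measure and no reason for stopping among the values supplied. It describes no ergometer test before the programme.

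**The concern.** Peak VO2, maximal workload and HRmax all rise if a patient works harder before the test ends. They measure fitness cleanly only if effort is comparable between arms. Here one arm has had three weeks of goals, feedback and encouragement, and the trial itself predicts that this arm will feel more confident about physical activity. Greater confidence is a plausible reason to push further at equal fitness.

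The two secondary outcomes are presented as separate benefits, one physical and one psychological. With these three values alone, a psychological effect that acts through effort is hard to tell from a physical one. This matters for the conclusion, because the Objective in the abstract counts better ergometer fitness among the results that would justify the technology.

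**Working it through.** **1. The plan's own figure.** The Sample Size Calculation section concerns daily steps: difference 2000, SD 3000, d = 2000/3000 = 0.67, alpha .05, power 90%, 50 per arm. Taking the test as two-sided (the article does not say), the exact t test needs 48.3 per arm, rounded up to 49, or 98 in total against the stated 100. Power at 50 per arm is 91.0%. The figure reproduces. It does not bear on the ergometer values, for which the article gives no SD, effect size or power.

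**2. Do the existing safeguards cover effort?**
- Assessor blinding protects against uneven encouragement by the tester. It does not equalise effort between patients who know their arm.
- Randomisation balances patients at allocation. An effort difference caused by coaching arises afterwards.
- Adjustment for confounders found afterwards cannot use an effort marker that was never obtained.
- HRmax carries some information about effort when compared between arms. The plan, however, analyses it as fitness, so extra effort would raise it and be counted alongside the other two.

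**3. Illustration of size.** Inputs from the article: 50 per arm and alpha .05. Assumed inputs: a two-sided test, no true fitness difference, and an effort-only shift of d standard deviations between arms.

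The noncentrality parameter is d × √(50/2) = 5d, with 98 degrees of freedom. The chance of p<.05 is the probability that the noncentral t exceeds the two-sided critical value.

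| Effort-only shift d | 5d | Chance of p<.05 |
|---|---|---|
| 0 | 0 | 5% |
| 0.1 | 0.5 | 7.9% |
| 0.2 | 1.0 | 16.8% |
| 0.3 | 1.5 | 31.8% |
| 0.4 | 2.0 | 50.8% |

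To express d as a percentage of the mean, a coefficient of variation is needed, and the article gives none. If it were 25% for peak VO2, then 0.1, 0.2 and 0.4 SD would be mean differences in the recorded peak value of 0.1 × 25% = 2.5%, 0.2 × 25% = 5% and 0.4 × 25% = 10%. These are differences in the value itself. They are not differences in pedalling time, which need not change peak VO2 in proportion.

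**The case against.** **The article is condensed.** Rules for ending a test and for handling submaximal tests may sit in the hospital's procedure, the full protocol or an analysis plan. That stands for those rules, and their absence is not the point here. But the article does fix which values are supplied, and a later analysis plan cannot use fields that were never requested.

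**The mechanism is not shown.** The article predicts higher self-efficacy. It does not say that this changes effort on an ergometer, nor does it describe how tests end, and staff may end some of them. The control arm is also active: it gets the same programme, planning exercise and booklet. This stands. The effort difference is a risk, and neither its existence nor its size is established.

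**The stakes are limited.** The primary outcome, accelerometer steps, is untouched. The authors say they do not strongly expect an effect on fitness. The Objective lists fitness jointly with more steps and higher self-efficacy, so a spurious ergometer result alone would not meet it. This also stands. On the other side, where the true effect is expected to be small, a modest effort difference could make up much of any difference seen.

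**Stronger readings that a reader might infer.** One is that the supplied data say nothing about effort. That goes too far, because HRmax compared between randomised arms is a blunted cue. Another is that medication makes HRmax useless as a check. The article says nothing about medication, and randomisation would balance it in expectation.

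**Conclusion.** The point holds as a weakness in how a secondary outcome is measured. The three values supplied are all effort-dependent, all three are labelled fitness, and patients are unblinded with motivational support in one arm only. An effort difference could therefore be reported as a fitness difference, and the plan obtains little with which to tell the two apart.

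The size is unknown. The figures of about 8%, 17% and 51% rest on assumed shifts of 0.1, 0.2 and 0.4 SD with no true difference. It would be wrong to read them as this trial's false-positive rate, because the article gives neither an ergometer SD nor any estimate of an effort difference. The primary analysis is not affected.

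**What to change.** In Primary and Secondary Outcomes, extend the data requested from the Cardiac Function Department to include, where recorded at the same test, peak respiratory exchange ratio, VO2 at the ventilatory threshold and reason for stopping. Measuring peak VO2 already requires gas exchange, so no further test is needed.

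In Statistical Analysis:
- Compare peak respiratory exchange ratio between arms in all tested patients.
- Report VO2 at the threshold as a supportive measure that depends less on effort.
- State in advance that a difference in peak VO2 or workload will be interpreted as fitness only if effort is similar between arms or the threshold measure agrees.
- Do not interpret HRmax as a fitness measure on its own.
- Avoid an analysis restricted to tests that reach a set respiratory exchange ratio, or label it descriptive. It selects patients on a variable measured after randomisation, and if effort differs by arm it no longer compares randomised groups.

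The cost is a longer data request and a little more analysis. Some threshold values will be missing because the threshold cannot be determined in every patient. The added fields also depend on what the test report contains, which the article does not show.
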